### Interventions

#### G-only

The gambling only Internet intervention will consist of a new online version of the self-change tools developed by Hodgins et al. [32]. These tools have shown a significant impact on gambling in three trials of the paper-based version of these materials [33–35], and have previously been translated successfully into an online format [26]. A major focus is to provide individuals with clear and concise behavioural and cognitive strategies for meeting the goal of reducing or quitting gambling. The various workbook sections are readily adaptable into online interactive formats.

#### G + MH

For participants in the G + MH condition, logging into the web portal will allow them to access the G-only Internet intervention as well as an online intervention for depression and anxiety. The mental health intervention chosen is MoodGYM, an extensively evaluated intervention found to be effective in a variety of different settings [36–38].

### Baseline assessment

The online assessment includes a demographic profile (age, gender, education, marital status, income, employment status) and a gambling, mental health and treatment history assessment. Problem gambling severity will be measured using the past year PGSI and the past three month version of the NORC DSM-IV Screen for Gambling Problems (NODS) which indicates DSM-IV severity [39, 40]. Hodgins [41] administered the NODS to problem gamblers as part of a 1-year follow-up after a brief treatment to assess its utility as a treatment outcome measure. Internal reliability was fair to good and the factor structure and item-total correlations supported the existence of a single higher order construct that correlated moderately with gambling behaviour and outcome. Prior treatment access will be measured using the items developed for previous trials conducted by Hodgins et al. [33, 34]. In addition, participants will be asked to identify a treatment goal (quit or reduced gambling) and how successful they think they will be (0 “not at all” to 10 “extremely”) in the next three months and in the next six months.

Severity of depressive symptoms will be measured using the PHQ-9 [42]. Severity of anxiety symptoms will be measured using the GAD-7 [43]. The Kessler 10 (K10) questionnaire will be included to provide a continuous measure of general psychological distress that is responsive to change over time. The K10 has been well validated and its brevity and simple response format are attractive features. It also produces a summary measure indicating probability of currently experiencing an anxiety or depressive disorder [29, 30].

Hazardous alcohol consumption will be measured using the Alcohol Use Disorder Identification Test Consumption measure (AUDIT-C) [44]. Illicit drug use will be assessed in a manor commonly used on general population surveys – by asking if the participant had used (from a list) any of the primary illicit drug categories ever, and in the last 12 months [45]. A more detailed assessment of illicit drug use is not warranted in this situation as the incidence of use will be too low for detailed analysis.

Quality of life will be assessed by the WHOQoL-8, an eight-item version of a widely used measure. This short form has been used in a number of countries, is robust psychometrically, and overall performance is strongly correlated with scores from the original WHOQoL [46].

### Follow-up assessments

Three and six months after randomization, an email invitation will be sent to participants containing a link to the follow-up assessment. Up to two reminder emails will be sent to promote retention in the trial. The follow-up will consist of an assessment of gambling behaviour, problem gambling severity (NODS), self-rated improvement, psychiatric distress, alcohol and illicit drug use, quality of life, and use of other treatment resources. Primary outcome measures will consist of problem gambling severity (as measured by the NORC DSM-IV screen for Gambling Problems (NODS – past 3-month version) [41], and mean days per month gambling in the past 3 months.

#### Use of interventions

We will have access to a complete record of the amount and type of use participants make of the G-only and G + GM interventions. This information will be used to test the moderation hypothesis that degree of involvement with the online gambling intervention is related to success at overcoming gambling problems. We will operationalize degree of involvement with G-only and G + MH interventions by recording the number of times the participant accesses the site as well as the number of modules completed and length of involvement with the site (e.g. use of the site over time).

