## Background

It is estimated that up to half of pathological gamblers have co-occurring mental health symptoms (e.g., depression or anxiety disorder) [1–6]. While there is little work in this area, co-occurring mental health symptoms are thought to impact on the treatment needs of problem gamblers [7–12]. The interrelationship between problem gambling and co-occurring mental health symptoms may not have the same cause for all those experiencing these co-occurring conditions. For some, gambling may be an attempt to alleviate the symptoms of depression and anxiety [13]. Others may experience symptoms of anxiety and depression as a result of increasing difficulties with gambling (financial or otherwise) [14]. For others, while occurring simultaneously, problem gambling and co-occurring mental health symptoms may not be causally related (or both might be the result of some third factor) [15]. In addition, it is important to consider the extent to which the interrelationship between problematic gambling and co-occurring mental health symptoms varies by gender – both in the strength of the observed relationship as well as in the underlying mechanisms that are driving this interrelationship [2, 16]. Further research employing longitudinal designs is needed to develop a better understanding of these interrelationships [5, 12, 17].

While the functional relationship of gambling to co-occurring mental health symptoms is an important research question, the goal of the present trial is a pragmatic one and, as such, does not need to wait upon a better understanding of these interrelationships. We seek to determine whether providing simultaneous access to online help for gambling problems and mental health symptoms is of benefit for those experiencing both concerns (and, to a lesser extent, that providing simultaneous access is not disadvantageous for those with just a gambling problem and no co-occurring depression or anxiety symptoms). A secondary goal will be to determine if there are moderators (e.g., gender, extent of use) for the hypothesized benefit of providing the G + MH intervention website to those problem gamblers with co-occurring mental health symptoms.

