## Major research questions

The proposed trial will compare two Internet intervention websites – an intervention that just targets gambling issues (G-only) versus one that contains interventions for anxiety and depression in addition to an intervention for gamblers (G + MH). The primary hypotheses are:**Hypothesis 1:** For problem gamblers with co-occurring mental health symptoms, it is predicted that participants provided access to the G + MH website will display significantly reduced gambling outcomes at three- and six-month follow-ups as compared to those provided access to the G-only website.**Hypothesis 2:** Problem gamblers without co-occurring mental health symptoms will display no significant difference between the G-only and G + MH websites at three- and six-month follow-ups.**Hypothesis 3:** Respondents who have more involvement with the G-only intervention between baseline and three-month follow-up will demonstrate more improvement in gambling outcomes at six-month follow-up, compared to respondents who have less involvement with the G-only intervention.

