### Data analysis

Analyses for Hypotheses 1 and 2, comparing outcomes between groups, will employ mixed effects repeated measures models that use all available data for each participant. Separate analyses will be conducted for each primary outcome variable. This same analytic approach, with the addition of interaction terms, will be used for secondary analyses examining moderators (e.g., extent of use, gender). Missing data will be handled using a maximum likelihood approach to estimate covariances, variances and means.

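### Hypothesis 3 compares self-selected heavier and lighter users of the website, yet it is listed as primary and called moderation, while elsewhere extent of use is a secondary moderator of the G + MH benefit

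*Protocol article*

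**What the plan says.** All places are in the protocol article.

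- **Major research questions.** Three hypotheses are introduced with "The primary hypotheses are". The third reads: "Respondents who have more involvement with the G-only intervention between baseline and three-month follow-up will demonstrate more improvement in gambling outcomes at six-month follow-up". Its comparison group is respondents with less involvement, not the other arm.
- **Use of interventions.** "This information will be used to test the moderation hypothesis that degree of involvement with the online gambling intervention is related to success". Involvement is to be measured by "recording the number of times the participant accesses the site as well as the number of modules completed", together with length of involvement, and is recorded for both websites.
- **Background.** "A secondary goal will be to determine if there are moderators (e.g., gender, extent of use) for the hypothesized benefit". The benefit meant is that of the G + MH website for gamblers with co-occurring symptoms.
- **Data analysis.** "Analyses for Hypotheses 1 and 2, comparing outcomes between groups, will employ mixed effects repeated measures models". Then: "This same analytic approach, with the addition of interaction terms, will be used for secondary analyses examining moderators (e.g., extent of use, gender").

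The status of extent of use therefore differs by section: primary as Hypothesis 3, secondary in the Background and in Data analysis. The question differs too. Hypothesis 3 asks whether use goes with improvement. The Background asks whether use alters the difference between arms.

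**The concern.** A moderator of a randomised comparison has to be fixed before randomisation, or at least be unaffected by it. Gender meets that condition and extent of use does not. Two separate problems follow.

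First, Hypothesis 3 has no randomised comparator. Motivated participants may both use the site more and gamble less, and someone who improves early may keep logging in. An association would then appear even if the website did nothing. Calling the test moderation, and listing it as primary, gives it a standing that randomisation does not support.

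Second, an arm-by-use interaction compares arms within levels of a variable observed after allocation. G + MH participants are offered the gambling tools plus MoodGYM, so total site use could plausibly differ by arm. Participants at the same level of use in the two arms need not then be comparable.

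At stake is how a positive result is interpreted, and whether a hypothesis whose status is unsettled could be promoted or demoted once data are seen.

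**Working it through.** **Inputs from the protocol article.** Power analysis: 280 participants, 20% attrition, about 224 followed at six months, α = .05. The attrition figure reproduces: 280 × (1 − 0.20) = 224.

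**Assumptions, not in the document.** Allocation is 1:1, giving 224 / 2 = 112 completers per arm, and tests are two-sided. All motivation correlations below are also assumed. The document gives none, so a range is shown.

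**Which participants does Hypothesis 3 cover?** It refers to involvement with the G-only intervention. That could mean the G-only arm (112). It could also mean everyone with access to the gambling tools (224), because the Interventions section gives those tools to both arms and the Abbreviations define G + MH as the G-only intervention plus MoodGYM. Both are computed.

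**Hypothesis 3 with no causal effect of use.** Let motivation correlate a with use and b with the six-month outcome, and let nothing else link the two. The correlation between use and outcome is then r = a × b. By Fisher's z, the chance of significance in the predicted direction is about

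Φ( atanh(r) × √(n − 3) − 1.96 ), with √109 = 10.44 and √221 = 14.87.

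| a, b | r | n = 112 | n = 224 |
|---|---|---|---|
| .3, .3 | .09 | Φ(0.94 − 1.96) = 15% | Φ(1.34 − 1.96) = 27% |
| .4, .4 | .16 | Φ(1.68 − 1.96) = 39% | Φ(2.40 − 1.96) = 67% |
| .5, .5 | .25 | Φ(2.67 − 1.96) = 76% | Φ(3.80 − 1.96) = 97% |

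Counting both tails changes the smallest entry only to 16%. The nominal rate is 5%.

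**Arm terms with no intervention effect.** A check used 2,000 simulated trials per setting, 112 per arm, ordinary least squares, and motivation correlating 0.5 with outcome. Rates of p < .05 were:

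| Motivation–use correlation (G-only, G + MH) | Shift in use under G + MH | Arm-by-use interaction | Arm effect given use | Arm effect, use ignored |
|---|---|---|---|---|
| .5, .5 | 0 | 4.5% | 3.8% | 3.8% |
| .5, .5 | 0.5 SD | 5.0% | 15% | 4.2% |
| .5, .5 | 1 SD | 4.6% | 42% | 4.9% |
| .5, .3 | 0.5 SD | 11% | 11% | 5.4% |
| .7, .3 | 0.5 SD | 34% | 16% | 5.3% |

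The interaction test keeps its error rate when motivation drives use equally in both arms, and loses it when the link differs. The arm effect conditional on use is distorted once the arm shifts use. The plain randomised comparison stays near 5% throughout.

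**The case against.** **A reader might infer that self-selected motivation will be reported as an intervention effect.** The document does not say so. Hypothesis 3 compares more with less involved respondents, and the Use of interventions section says only that involvement is related to success. Both are associational wordings, and if use and outcome do correlate, an associational hypothesis is true. The percentages for Hypothesis 3 therefore count as errors only under a causal reading. The primary listing, the word moderation and the Background's reference to benefit invite that reading without stating it.

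**A reader might also infer that the arm-by-use interaction is biased as a matter of course.** The simulation does not support that: error stays near 5% when motivation drives use equally in both arms. Nor is it established that the arm changes use of the gambling tools, which both arms receive. The argument is stronger if total site use is the measure, and the text leaves that open.

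**Timing.** Use is taken up to three months and outcome at six. This limits the route through early success but does not close it. Improvement is judged from baseline, so early gains can affect both continued use and the later result. Motivation precedes both.

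**Simplicity of the model.** The calculation is a plain correlation with the six-month outcome, whereas the planned approach is a repeated measures model. It shows the order of size and does not forecast the trial's own analysis.

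**Condensed article.** The model and covariates for Hypothesis 3 may stand in an analysis plan that is not shown, so their absence is not held against the protocol. What stands is what the text does state: conflicting status, a moderation label for an unrandomised contrast, and a post-randomisation variable placed beside gender in interaction tests.

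**Conclusion.** The point holds in this form. The article gives Hypothesis 3 primary status in one section and extent of use secondary status in two others. It calls an observational association moderation, and it plans an arm comparison conditional on a variable that participants determine after randomisation.

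For Hypothesis 3, if it is taken as evidence that use helps, motivation alone would produce a significant result in about 15% to 76% of trials with 112 completers, or 27% to 97% with 224. This rests on assumed correlations of .3 to .5 with both use and outcome and on no causal effect. For the arm-by-use analysis, bias is conditional: it requires that the arm changes use or that the motivation–use link differs by arm, and neither is known.

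The randomised comparisons in Hypotheses 1 and 2 are untouched, so this should be corrected but does not threaten the main between-arm results.

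**What to change.** 1. Reconcile Major research questions, Background and Data analysis by making Hypothesis 3 secondary, and state whether it covers the G-only arm or all participants with access to the gambling tools.
2. In Use of interventions, replace the moderation label with an association between use and outcome, and state that it does not estimate an intervention effect.
3. Adjust that association for baseline severity (NODS or gambling days), treatment goal, expected-success rating, K10 and prior treatment. The Baseline assessment section already covers these, so no new data are needed. Say that adjustment reduces confounding but does not remove it.
4. Restrict arm-interaction moderators to baseline variables such as gender, and drop extent of use from that list.

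The cost is some rewording and a covariate list. The downside is that Hypothesis 3 can no longer be claimed as a primary result.

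A complier-type estimate of the effect of MoodGYM use, with randomised arm as instrument, is optional and not part of this fix. It answers a different question from Hypothesis 3 and would be imprecise. It also needs the exclusion restriction that arm affects gambling only through MoodGYM use, which would be doubtful if arm also changes use of the gambling tools.

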### Power analysis

We propose to collect a sample of 280 participants and we estimate that we will successfully follow about 224 participants at six months (20 % attrition) [34]. This number will also provide sufficient power to conduct the proposed statistical tests comparing hypotheses, based upon gambling frequency and NODS data from Hodgins et al. [33, 34], assuming a correlation of .5 between baseline and follow-up values, power = .80 and an α = .05. This sample size will be sufficient to detect a difference of about two gambling days per month between conditions at each follow-up interval. Smaller differences may not be clinically important. Similarly, this sample size will be sufficiently powered to detect a 1 point difference on the NODS at six months. These calculations are based upon a repeated measures ANOVA model. The proposed analyses will employ mixed effects repeated measures models and, as such, will have greater statistical power because all observed data are included.

Also important is to ensure that there are enough females in the sample to conduct the proposed sex difference analyses. Approximately a third of problem gamblers in the general population are female [47]. With the assumption that this proportion would be maintained in our sample (i.e., those who would be concerned about their gambling and agree to participate in the study), roughly 92 of the 280 respondents will be female. A sample with 23 respondents per condition is sufficiently large to conduct the proposed analyses. However, our experience using these same recruitment methods in other studies is that females tend to be more interested in self-help materials than males and also, to be willing to participate in the proposed research. Thus, we fully anticipate that more than a third of respondents will be female (perhaps as many as half will be female if the recruitment trends in our other studies hold true with this trial as well).

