#### Inclusion criteria

Primary inclusion criteria will follow those used in the ongoing trial by Hodgins et al. [26] and comprise being 18 years of age or older, perception of a gambling problem and scoring 3 or greater on the Problem Gambling Severity Index (PGSI) [28]. Prior treatment access will be measured but will not be used as an inclusion/exclusion criterion. This is because the intent of this trial is to evaluate the impact of the interventions in the extended range of potential community participants. Random assignment to condition with stratification will ensure that socio-demographic characteristics, such as treatment access, will be evenly distributed across conditions. Similarly, hazardous alcohol use and illicit drug consumption will be measured but will not be used as exclusion criteria. Finally, the trial will recruit participants with and without co-occurring mental health symptoms. We anticipate, based on prevalence data, that approximately 50 % of the sample will be experiencing co-occurring mental health symptoms. This will be established using the Kessler 10, with a score of 22 more indicating current psychological distress [29, 30].

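### The 80% power is worded for the whole sample, but Hypothesis 1 is tested in about half of it; if the wording is literal, power for that test is about 51%

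*Protocol article*

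**What the plan says.** **Power analysis.** The sample is set out as "We propose to collect a sample of 280 participants and we estimate that we will successfully follow about 224 participants at six months (20 % attrition". The settings are "assuming a correlation of .5 between baseline and follow-up values, power = .80 and an α = .05". Two conclusions follow: "This sample size will be sufficient to detect a difference of about two gambling days per month between conditions at each follow-up interval", and for the second primary outcome, "this sample size will be sufficiently powered to detect a 1 point difference on the NODS at six months". The SDs are referred to earlier trials and not printed. No n per group is given for this calculation, and the symptom subgroup is not named.

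**Major research questions.** Hypothesis 1 is confined to one group: "For problem gamblers with co-occurring mental health symptoms, it is predicted that participants provided access to the G + MH website will display" better gambling outcomes than those given the G-only website. Hypothesis 2 concerns the complementary group and predicts no significant difference. No hypothesis compares the two arms in everyone.

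**Inclusion criteria.** The authors expect that about 50% "of the sample will be experiencing co-occurring mental health symptoms", defined by a K10 score of 22 or more.

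**Power analysis, second paragraph.** For the sex analyses, roughly 92 women become 23 per *condition*. That is 92/4, not 92/2.

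**The concern.** The detectable differences are attached to the total sample, while the trial's central hypothesis uses about half of it. Halving the n per arm inflates the standard error by √2, so power that is adequate for everyone is not adequate for the subgroup.

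Nor does the whole-sample figure answer another stated question. Under the authors' own predictions (a benefit with symptoms, none without), a 2-day benefit in half of the sample averages to 0.5 × 2 + 0.5 × 0 = 1 day overall.

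What is at stake is how a non-significant Hypothesis 1 result is read. The section treats differences below about two days as possibly unimportant clinically. A reader told that power for two days is .80 would take a null result as fair evidence against adding the mental health intervention. If the true power is nearer one half, that inference fails.

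**Working it through.** **Inputs from the article**
- 280 enrolled, 20% attrition: 280 × 0.8 = 224, which reproduces the printed figure.
- Power .80, α = .05, baseline to follow-up correlation .5.
- Differences of 2 days per month and 1 NODS point.
- Subgroup share about 50%.

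**Assumptions, because the article does not state them**
- Two-sided α and 1:1 allocation.
- The same attrition in both symptom groups.

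**Group sizes**
- Whole sample: 224/2 = 112 per arm.
- Hypothesis 1: 224 × 0.5 = 112 followed, so 56 per arm.

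**The plan's own power.** It cannot be reproduced independently, because no SD is printed. It can only be back-solved. With z = 1.960 + 0.842 = 2.802, 80% power requires an analysis-scale SD of difference / (2.802 × √(2/n)). Dividing by √(1 − .5²) = √.75 gives the raw SD under baseline adjustment.

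| n per arm | analysis-scale SD, days / NODS | raw SD, days / NODS |
|---|---|---|
| 112 | 5.34 / 2.67 | 6.17 / 3.08 |
| 56 | 3.78 / 1.89 | 4.36 / 2.18 |

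**Reading A: the 80% refers to all 224.** Keep the SD fixed and reduce n by the subgroup share s. Power = Φ(2.802 × √s − 1.960), and the SD cancels.
- s = 0.5: Φ(1.981 − 1.960) = Φ(0.021) = 0.508 (0.502 by noncentral t).
- s = 0.4: Φ(1.772 − 1.960) = 0.425.
- s = 0.6: Φ(2.170 − 1.960) = 0.583.
- Differences detectable with 80% power at s = 0.5: 2 × √2 = 2.83 days and 1 × √2 = 1.41 NODS points.
- One-sided α throughout, s = 0.5: 0.545.
- All 140 enrolled subgroup members contribute (70 per arm): Φ(2.802 × √(70/112) − 1.960) = 0.601.

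**Reading B: the calculation used four arm-by-symptom cells of 56.** Power for Hypothesis 1 is then 80% by construction, and a whole-sample comparison would have Φ(2.802 × √2 − 1.960) = 0.977. This holds only if the raw SDs are no larger than those in the second row of the table.

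**Which reading holds depends on the SD.** For a 2-day difference, baseline-adjusted with r = .5, over assumed raw SDs:

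| raw SD, days | power at 112 per arm | power at 56 per arm |
|---|---|---|
| 4 | 99.1% | 86.3% |
| 5 | 93.3% | 68.6% |
| 6 | 82.1% | 53.1% |
| 7 | 69.5% | 41.5% |

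**The case against.** The strongest reply is that the authors may have sized the subgroup test all along. The section says that the sample gives enough power for the tests proposed, and the tests for Hypotheses 1 and 2 are both within subgroups. The only per-group count in the section, 23 women, is 92 divided by four. The same division of 224 gives 56, exactly the Hypothesis 1 group size. This stands as a real possibility, and it is why 51% can be given only conditionally. It does not settle the matter. The figure of 23 belongs to a different paragraph and starts from enrolled rather than followed numbers. Elsewhere the article uses *condition* for the randomised website. The SDs that Reading B needs are not shown.

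Second, an article may leave SDs to a fuller document. Agreed: their absence alone is not the point. The point is a printed power figure whose wording covers a comparison that no hypothesis makes.

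Third, sufficient power may mean more than 80%, and the planned mixed model uses all observed data. The section states .80 as its planning value, so that is the figure to test. Even with data from all 140 subgroup members, power under Reading A is 60.1%. Any further gain from two follow-ups is not quantified.

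A reader might also infer that 50% is a ceiling on the subgroup share, since the Background says: "It is estimated that up to half of pathological gamblers have co-occurring mental health symptoms". That does not follow. The Background sentence concerns estimates in pathological gamblers. The trial's planning figure is its own expectation of about 50% above a K10 cut-off among its recruits. A range on both sides of 50% is the fair sensitivity check.

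**Conclusion.** The concern holds in conditional form. As worded, the 80% power for about two days and 1 NODS point describes the total sample, and 80% power for Hypothesis 1 is not shown. If the figure does refer to all 224 followed, power for Hypothesis 1 is about 51%, or about 43% to 58% for a share of 40% to 60%. This rests on 80% being exact at 112 per arm, a two-sided test, equal allocation and even attrition.

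A reader might go further and conclude that Hypothesis 1 definitely has only even odds of detecting its target. The article does not support that: no SD is printed, and the four-cell reading, under which 80% would be correct, is not excluded. Nor is a printed number miscalculated. The fault is that the stated power is not tied to the comparison the trial is built on.

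**What to change.** Restate the power paragraph for the Hypothesis 1 comparison: name the subgroup (K10 of 22 or more), the followed n per arm (about 56) and the SDs used for days and NODS. Then:
- If the calculation was on the whole sample, replace the figures with about 2.8 days and 1.4 NODS points at 80% power, or state about 51% power for 2 days and 1 point.
- If it was on 56 per arm, say so; the printed SDs will then support the existing figures.
- Use *condition* in one sense throughout the section.
- State that a non-significant Hypothesis 1 result will be interpreted by its confidence interval.

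This is a change of wording and needs no extra enrolment. The cost is that the stated figure may become less favourable.
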